### Outcomes

The primary outcome, to identify the RP2D, is based on:

Safety: The highest dose level that has an estimated probability of DLE closest but below the target DLE level of no greater than 33%. The totality of the safety data will also be considered.PK: Achieving and maintaining putative melatonin plasma levels of at least 15–30 mg/L and ensuring BAC remains <0.25 g/L. The PKPD (dose-response curve stratified by severity of HIE) model may also be considered.

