The DSMB will review the safety and PK data following the recruitment of the third baby in a cohort. The DSMB will recommend to the Trial Steering Committee (TSC) one of the following possible outcomes: (1) Recruit at the next dose level, (2) Continue recruitment at the current dose level, (3) Reduce dose to one of the previous dose levels (where relevant), or (4) Stop the trial. Dose escalation decisions will be based on both the concurrent accumulating safety (suspected DLEs) and PK data, and their predictions at the next dose level. For PK, the trial pharmacologist will develop a population-PK model to simulate the plasma melatonin levels and BACs at the next dose level. If PK modelling predicts that melatonin systemic exposure will be equal to or exceed the Cmax of 33.5 mg/L and Area under the serum concentration vs. time curve for 0-24h (AUC24) of 454.7 mg*h/L or the BAC safety threshold (<0.25 g/L), that dose level will not be opened to recruitment. For DLE predictions, a Bayesian Escalation with Overdose Control (EWOC) approach will be used. EWOC uses a statistical model to estimate the risk of DLE per dose level with the target level of DLEs set at 33% for this trial. While awaiting dose escalation decisions (from the second dose level onwards), and in the absence of DLEs in the first three babies, a maximum of three further babies can be recruited to the current dose level after approval from the DSMB. In the event of a DLE, or having recruited the three additional babies, backfilling^40^ to the previous dose level can occur while awaiting the dose escalation decision. Data acquired from additional babies will be included in a subsequent dose escalation report for review by the DSMB/TSC. Backfilling will be limited to a maximum of 15 babies in the dose escalation study.

The subsequent dose escalation will proceed to dose level 2 at a loading dose of 10 mg/kg and maintenance doses of 5 mg/kg. Subsequent doses for dose level 3 and dose level 4 will be determined by the safety and PK model prediction. Provided that dose levels 1 and 2 have not exceeded the maximum BAC safety threshold and no other dose-limiting toxicity is encountered, further escalation will be recommended. Using the parameters of a population PK model, dose escalation will be evaluated. The possible scenarios are:

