### Sample size and statistical analysis

This is a dose-finding, safety study. The sample size of 60 participants is based on the collection of sufficient safety data to estimate the risk of DLE and PK profile at each dose level, plus a cohort expansion cohort to assess recruitment feasibility within the time targets of the trial.

The escalation will proceed according to the principles of the Bayesian Escalation with Overdose Control (EWOC) approach. The maximum tolerated dose (MTD) is defined to be the dose level of melatonin that results in a probability θ=33% that a DLE will occur in the period between the initiation of IMP treatment and 100 hours after the final administration of IMP, that is, P (DLT | dose = MTD) = 33%. The expected proportion of babies treated at doses above the MTD will be controlled at a maximum of 25% (EWOC feasibility bound α, kept constant). We use the classical specification of EWOC with a two-parameter logistic curve between dose and probability of DLE .^68^ The two parameters of the re-parameterised model, γ (the MTD) and ρ (the probability of DLT at the dose level 1), are given Uniform (ie, β (1,1)) prior distributions. For γ, the range is from the lowest dose to the highest dose. For ρ the range is from 0% to θ=33%.

We will use cohorts of three patients during the dose escalation part of the study. The operating characteristics of the dose-finding design are based on DLE occurrence for three key scenarios, based on 1000 simulations of the study per scenario (see table 5) for 24 dose-finding babies in cohorts of three. The first scenario is such that the MTD is expected to be the fourth dose level (ie, γ=4) and ρ=0.1. The second scenario is one where the fourth dose level is too toxic (P (DLE | dose=4) = 51%) and the MTD is the third one. In the third scenario, the probability of DLE is generally high (ρ=0.15, P (DLE | dose=4) = 79%), and the MTD is the second dose level.

**Table 5 T5:** Operating characteristics of the Bayesian Escalation with Overdose Control (EWOC) approach

	First dose level	Second dose level	Third dose level	Fourth dose level
DLE Curve				
Scenario 1; DLE probability	0.10	0.15	0.23	0.33 (MTD)
Scenario 2; DLE probability	0.10	0.19	0.33 (MTD)	0.50
Scenario 3; DLE probability	0.15	0.33 (MTD)	0.58	0.79

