Recommendation percentages (1000 repetitions). The proportions are the percentage of the simulations that recommended each dose level. For example, in scenario 1, dose level 3 was recommended in 69% of the simulated trials.				
Scenario 1; recommendation (%)	0.0	28	69	3
Scenario 2; recommendation (%)	2	50	48	0
Scenario 3; recommendation (%)	10	89	1	0

DLE, dose-limiting event; MTD, maximum tolerated dose.

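### Table 5's recommendation rates cannot come from the RP2D safety rule under Outcomes, because that rule can never select the fourth dose level

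*Protocol article*

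**What the plan says.** **Outcomes (Protocol article).** The safety part of the RP2D is "The highest dose level that has an estimated probability of DLE closest but below the target DLE level of no greater than 33" per cent. The section adds "The totality of the safety data will also be considered" and sets PK conditions beside it.

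**Dose escalation procedure.** The DLE risk at each level is a model estimate: "EWOC uses a statistical model to estimate the risk of DLE per dose level".

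**Sample size and statistical analysis.** "The maximum tolerated dose (MTD) is defined to be the dose level of melatonin that results in a probability θ=33" per cent. The expected share of babies treated at "doses above the MTD will be controlled at a maximum of 25" per cent. On the model: "We use the classical specification of EWOC with a two-parameter logistic curve between dose and probability of DLE". Its two parameters are γ (the MTD), with a uniform prior from the lowest to the highest dose, and ρ (the DLE risk at level 1), uniform from 0 to 33%.

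**Table 5.** Results are for 24 babies in cohorts of three, 1000 simulations per scenario, on DLE occurrence alone. "The proportions are the percentage of the simulations that recommended each dose level". The level whose true risk is 0.33 is marked as the MTD: level 4, 3 and 2 in scenarios 1, 2 and 3. The rule that produced a recommendation is not stated.

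**The concern.** Identifying the RP2D is the primary outcome, and the RP2D is the dose given to the 21–36 babies of the expansion cohort. Table 5 is the only published evidence of how well the DLE part of that decision performs. If its recommendations were made by a different rule from the one under Outcomes, the printed selection rates do not describe the decision the trial says it will make.

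There is a second consequence. If the stated rule and the stated prior together exclude the top level whatever the data show, then scenario 1, where the top level is the marked MTD, cannot be answered correctly under the stated rule.

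**Working it through.** **Inputs (Sample size and statistical analysis; Table 5).** θ = 0.33; γ uniform on levels 1 to 4; ρ uniform on 0 to 0.33; 24 babies in cohorts of three; EWOC bound 25%. Reading γ's range as levels 1 to 4 follows the simulation text, which works in level numbers (γ = 4, dose = 4).

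**Step 1: reproduce the DLE curves.** The model is

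logit P(x) = logit ρ + (logit θ − logit ρ)·(x − 1)/(γ − 1), with logit 0.33 = −0.708.

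- Scenario 1 (ρ = 0.10, γ = 4): logit 0.10 = −2.197, slope (−0.708 + 2.197)/3 = 0.496, giving 0.10 / 0.154 / 0.231 / 0.33.
- Scenario 2 (ρ = 0.10, γ = 3): slope 1.489/2 = 0.745, giving 0.10 / 0.19 / 0.33 / 0.509.
- Scenario 3 (ρ = 0.15, γ = 2): logit 0.15 = −1.735, slope 1.026, giving 0.15 / 0.33 / 0.579 / 0.793.

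These match Table 5 to rounding (scenario 2, level 4 is 0.50 in the table and 51% in the text).

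**Step 2: what the prior allows at level 4.** Put x = 4. Since γ ≤ 4, (x − 1)/(γ − 1) = 3/(γ − 1) ≥ 1. Since ρ ≤ θ, logit θ − logit ρ ≥ 0. Hence logit P(4) ≥ logit θ, so P(4) ≥ 33% for every (γ, ρ) in the prior. A posterior mean, posterior median or plug-in value at level 4 is therefore never below 33%; the lowest reached in simulation was 0.36–0.38. A below-33% rule recommends level 4 in 0% of trials.

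**Step 3: compare with Table 5.** Scenario 1 prints 0 / 28 / 69 / 3. With 1000 repetitions, 3% is about 30 trials, with standard error √(0.03 × 0.97/1000) ≈ 0.5 points. It is not a rounded zero.

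**Step 4: size of the mismatch.** Trials were simulated with the inputs above, starting at level 1, with allocation by the 25th percentile of γ rounded to the nearest level (10,000 trials per scenario). Several final rules were applied to the same data. Entries are % recommended at levels 1/2/3/4. The last column is the total absolute deviation from Table 5 over its 12 cells, in points.

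| Final rule | Scenario 1 | Scenario 2 | Scenario 3 | Deviation |
|---|---|---|---|---|
| Table 5, printed | 0/28/69/3 | 2/50/48/0 | 10/89/1/0 | – |
| 25th percentile of γ, nearest level | 0.6/31.2/67.5/0.7 | 1.2/52.3/46.5/0 | 11.3/84.7/4.0/0 | 21 |
| Highest level, posterior mean < 33% | 0.9/42.0/57.2/0 | 2.4/65.9/31.8/0 | 27.1/71.9/1.0/0 | 96 |
| Highest level, posterior median < 33% | 0.7/34.7/64.6/0 | 1.7/58.6/39.8/0 | 18.5/79.0/2.5/0 | 52 |
| Highest level, plug-in < 33% | 0.5/33.8/65.7/0 | 1.2/57.0/41.7/0 | 11.4/85.9/2.7/0 | 33 |

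The percentile rule is the closest of those tried, but it is not an exact match: 0.7% against 3% at level 4 in scenario 1, and 84.7% against 89% at level 2 in scenario 3.

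Against that inferred rule, the below-33% rule chooses a different level in about 12–19% of trials with the posterior mean, 4–9% with the posterior median and 3–6% with plug-in estimates. The ranges span the three scenarios and repeated runs.

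**Step 5: a very safe drug.** With an assumed flat DLE risk of 2% at all levels, the percentile rule picks level 4 in about 61–62% of trials. The below-33% rule picks level 3 in 100% and level 4 in 0%, with all three estimators.

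**Step 6: the other reading of γ's range.** If γ is allowed to reach dose 6 of Table 1, every rule tried misses Table 5 by at least 127 points in total. This supports the four-level reading.

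**The case against.** Only one RP2D safety rule is printed, and using an EWOC quantile for escalation with a point estimate for the final choice is ordinary practice. Table 5 is presented as describing the dose-finding design on DLEs alone, while the RP2D also rests on PK, the totality of safety data, and DSMB and TSC review. The choice of estimator is commonly left to the SAP.

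Much of this stands, and it limits the point:

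- A reader might infer that the protocol contains two competing RP2D rules. It does not print a second one. Table 5's rule is inferred, and the best candidate reproduces the table only approximately.
- A reader might take the largest gap as the finding: scenario 3 with the posterior mean, about 27/72 at levels 1 and 2 against 10/89 printed. With plug-in estimates the same rule gives about 11/86, and the contrast almost vanishes. The protocol names no estimator, so neither figure can be called its own.
- A reader might also infer that Table 5's rule always picks the higher dose. With plug-in estimates the below-33% rule picked the higher level in about 2% of scenario 3 trials.
- Nor do the documents support saying that an analyst may freely choose either dose, or that a target below 33% contradicts an MTD defined at 33%. Taking the nearest level below a continuous MTD is a normal way to discretise it.

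What does not fall is Step 2 set against the 3% cell. It needs no simulation and no choice among mean, median and plug-in. One narrow escape remains. An estimate placed exactly on the boundary γ = 4, such as a posterior mode, gives exactly 33% at level 4. It would pass if the phrase about being no greater than 33% overrides the word below. The Outcomes sentence contains both, which is a further reason to settle the wording.

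**Conclusion.** The point holds. Table 5's recommendation percentages are not those of the Outcomes rule as worded, and under the stated prior that rule excludes the top simulated level however clean the DLE data are. This rests on γ's range ending at level 4 in the simulation and on the DLE risk being a model estimate, as the protocol says.

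The practical size is less certain. Selection of the marked MTD under the Outcomes rule is 0% against 3% printed in scenario 1, about 31–42% against 48% in scenario 2, and 71–86% against 89% in scenario 3, depending on the estimator. The disagreement rates of 3–19% are relative to an inferred rule and should be read as indicative only.

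This is a moderate, easily repaired fault in the published operating characteristics of the primary decision. It does not show that the escalation scheme itself is unsound.

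**What to change.** Before the first dose-escalation review, reconcile Outcomes with Sample size and statistical analysis:

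1. State one final safety rule for the RP2D, giving the estimator, the threshold (strictly below, or no greater than, 33%) and how a continuous value is rounded to a level. Make it compatible with γ's prior range and use it in both sections.
2. Re-run Table 5's recommendation rows under that rule, and mark as correct the level that the rule targets.
3. If the below-33% rule is kept, either extend γ's prior above the top level or state that the top level cannot be selected on the model estimate. If the simulated rule is kept, print it and align the Outcomes sentence with it.

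The cost is one sentence and a re-run of existing code. The printed rates will change in both directions. For example, if the correct choice becomes the highest level with true risk below 33% (levels 3, 2 and 1), the posterior-mean rule selects it in about 57%, 66% and 27% of trials, against 3%, 48% and 89% now printed at the marked MTDs.

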### Dose-limiting events

Suspected DLEs are defined as any events listed below considered *related* to the IMP by the attending neonatologist and site investigator:

Severe AE defined by any single event that is grade 3 and above on the NAESS^39^Serious AE (SAE)

In the event that a suspected DLE occurs, the sponsor will be notified within 24 hours and the event will be reviewed by an independent clinical reviewer. The DSMB will review the data to confirm the DLE and advise on whether to continue recruitment at the same dose level or recruit to a lower dose level. If a suspected DLE occurs in a *sentinel* baby, at the discretion of the DSMB and TSC, a second *sentinel* baby may be requested at the same dose level; however, if a further suspected DLE occurs in this second *sentinel* baby, the dose will be considered unsafe, and no further dosing will occur at this dose level or higher.

### Participant timeline

The infusion of the loading dose of IMP will be given as soon as possible after birth (T0), once arterial and venous access has been obtained and the participant is deemed clinically stable. IMP must be administered no later than 6 hours after birth with five subsequent maintenance doses given at T0+24 hours, T0+36 hours, T0+48 hours, T0+60 hours and T0+72 hours (±1 hour) via an individual lumen of a well-placed central venous catheter or peripheral venous cannula. Screening for clinical stability, assessments and investigations will be performed in accordance with the schedule of events summarised in table 2 with a detailed schedule outlined in the supplementary materials (online supplemental table S3). Clinical stability must be confirmed within 30 mins prior to each scheduled IMP administration. Further clinical safety data during the infusion of the IMP will be collected as outlined in table 3. This includes intensive vital signs (including invasive blood pressure) monitoring every 15 mins during the loading dose, liberalising to every hour during the maintenance doses. In the event that invasive blood pressure monitoring is lost after T0+48 hours, IMP administration may continue provided the baby is not on inotropic support and has not experienced a DLE.

**Table 2 T2:** Summary schedule of events

Schedule of events	Screening and T0	T0+ 24 hours (±1 hour)	T0+ 36 hours (±1 hour)	T0+ 48 hours (±1 hour)	T0+ 60 hours (±1 hour)	T0+ 72 hours (±1 hour)	T0+day 7 (±1 day)	Hospital discharge
Informed consent	X							
Eligibility	X							
Clinical stability	X	X	X	X	X	X		
Baby demographics	X							
Maternal characteristics	X							
Pregnancy and delivery history	X							
Placental histology	X							
Physical examination	X							
Therapeutic hypothermia	X	X	X	X	X	X		
IMP administration	X	X	X	X	X	X		
Cranial ultrasound with resistance index	X	X		X		X		
aEEG/EEG	X	X	X	X	X	X		
NIRS	X	X	X	X	X	X		
Modified Sarnat neurological examination	X	X		X		X	X	X
Concomitant medications	X	X	X	X	X	X	X	X
Review of AE and SAEs	X	X	X	X	X	X	X	X
Cord/blood gas pH/base deficit	X							
Biochemistry (renal, liver profile, CRP, troponin, CK, LDH)	X	X		X		X		
Blood culture	X							
Blood gas	X	X		X		X		
Full blood count	X	X		X		X		
Clotting including fibrinogen	X							
MRI/MRS neuroimaging								
Hammersmith Neonatal Neurological Examination (HNNE)								X
Hearing screen								X
Discharge characteristics								X
General movement assessment								X

The full detailed schedule is included in the supplementary materials (online supplemental table S3).

AE, adverse event; aEEG/EEG, amplitude-integrated electroencephalography; CK, creatine kinase; CRP, C-reactive protein; IMP, investigational medicinal product; LDH, lactate dehydrogenase; MRS, magnetic resonance spectroscopy; NIRS, near infrared spectroscopy; SAE, serious adverse event.

**Table 3 T3:** Vital signs monitoring during IMP administration

	During the loading dose (initiation of infusion = L0)		During the maintenance dose (initiation of each infusion = M0)	
	Every 15 mins during the 2-hour loading dose infusion (L0 to L0+2 hours)	At L0+6 hours, 12 hours, 18 hours and 24 hours (L0+2 hours to L0+24 hours)	Every 1 hour during the maintenance doses (M0 to M0+2 hours)	At M0+6 hours and M0+12 hours (M0+6 hours to M0+12 hours)
Mean arterial blood pressure*	X	X	X	X
Core temperature	X	X	X	X
Ventilation (mode, FiO_2_ requirement)†	x	X	X	X
Cerebral NIRS rSaO_2_	X	X		
Heart rate	X	X	X	X

* In the event that invasive arterial access is lost after 48 hours from the start of the loading dose (L0+48 hours), provided there is no DLE and the baby is not on inotropic support, melatonin may be continued and non-invasive blood pressure monitoring recorded.

† Ventilation data will be recorded every 30 mins during the loading dose.

DLE, dose-limiting event; FiO2, fraction of inspired oxygen ; IMP, investigational medicinal product; NIRS, near infrared spectroscopy; rSaO2, regional oxygen saturation.

Blood (PK) samples will be obtained (0.5 mL in sodium fluoride/potassium oxalate) at T0, T0+2 hours, T0+24 hours, T0+26 hours, T0+48 hours, T0+96 hours to measure peak and trough melatonin and BAC levels. Parents, guardians and those legally responsible for the participant may also give consent to the exploratory biomarker study outlined in figure 3 with the schedule of blood sampling shown in table 4. Where available, all samples will be obtained from the arterial line; however, if this is no longer available after T0+48 hours, the PK sample must be obtained via venepuncture. The exploratory biomarker sample may be obtained opportunistically with routine bloods. Where the participant is anaemic (haemoglobin (Hb) <100 g/L), the exploratory biomarker sample must not be taken. Standard-of-care blood results (full blood count, renal and liver profiles, coagulation screen, blood culture, CRP) will also be collected as part of the trial.

**Table 4 T4:** Exploratory blood biomarker sample schedule

Sampled	Screening /baseline	T0+24 hours (+12 hours)	T0+48 hours (+12 hours)	T0+72 hours (+12 hours)	T0+96 hours (+12 hours)
Blood plasma sample (1 mL in EDTA)	X	X	X	X	X
Dried blood spot for microRNA (80 uL of whole blood)	X	X	X	X	X
Point-of-care GFAP/UCH-L1 (10 uL of whole blood)	X	X	X	X	X

GFAP, glial fibrillary acid protein; UCH-L1, ubiquitin carboxyl-terminal hydrolase L1.

Following completion of AE monitoring and neonatal intensive care, babies will be discharged with outpatient follow-up at 3 months. Prior to discharge, neurological assessments including the Hammersmith Neonatal Neurology Examination and video for General Movement Assessment will be performed as part of standard care as shown in table 1. At follow-up, the Ages and Stages Questionnaire, the Hammersmith Infant Neurological Examination and a further General Movement Assessment video will be obtained.

### Data collection and management

Participants meeting the eligibility criteria for the ACUMEN Trial will be enrolled via the Sealed Envelope online system, which will allocate participants to an individualised participant identification number (PIN) for pseudo-anonymisation of research data. During the dose escalation phase, assignment to the current dose level will be managed via the Sealed Envelope system in accordance with the dosing schedule approved by the TSC. Clinical data from participant records will be collected as illustrated in the schedule of events (see table 2) under the PIN into the password-protected study database (OpenClinica). MRI/MRS Digital Imaging and Communications in Medicine (DICOM) data will be transferred to VoxelFlow software, anonymised and reviewed by two independent experts in perinatal brain MRI interpretation. The aEEG/EEG recording will be uploaded to the Stratus EEG system software for review by a neurophysiologist with expertise in neonatal neurology. Where available, the NIRS trace will be transferred to the UCL Data Safe Haven for review. Laboratory data (including PK) will be provided directly to the sponsor. All PK final reports will be entered into OpenClinica linked to the PIN.

All data will be handled in accordance with the Data Protection Act 2018 and the EU General Data Protection Regulation (GDPR) 2016. The data are stored on secure, GDPR-compliant, cloud-based servers held within the UK and EU. Any transfer of documentation containing personally identifying data between the site and the coordinating centre will be subject to AES-256 industry-standard encryption.

### Analysis of biological samples

The plasma levels of melatonin, ethanol and acetaldehyde will be measured by a central Good Laboratory Practice (GLP) laboratory (Analytical Services International (ASI), London); plasma melatonin levels will be measured using liquid chromatography-tandem mass spectrometry (LC-MS/MS), ethanol and acetaldehyde levels will be measured using headspace gas chromatography-flame ionisation detection (Headspace GC-FID).

Whole blood UCH-L1 and GFAP concentration will be measured in real time at the cot side using the Abbott Traumatic Brain Injury cartridge and Alinity POCT device according to the manufacturer’s instructions. All plasma and dried blood spots will be processed at the local sites, stored at −80°C and transferred to the UCL Neonatal Neuroprotection Research Group Laboratory for biobanking at the end of the study. Plasma protein concentrations will be measured using the Alamar NULISA Central Nervous System Disease panel array by the UCL Dementia Research Institute Biomarker Factory. Qiagen will measure an array of microRNA markers previously shown to have predictive potential in HIE.^45^ Plasma metabolomics will be measured using non-targeted rapid liquid chromatography mass spectrometry analysis by Sapient Bioanalytics. The remaining samples will be stored for future exploratory biomarker studies.

